**Questionnaires**				

Sociodemographics	X		X	X
Age, sex, race/ethnicity, education, income, employment^1^, health insurance^1^, financial stress^¶^				

Attitudes, beliefs, and other behavioral measures	X	X	X	X
Trust in health professionals, preferred role in decision-making, depression treatment preferences, spirituality, respect, perceived involvement in care^2^, racial identity, social support, life events				

Health Status	X	X	X	X
Physical and mental, measured by MOS-SF12, CIDI^3 ^&ES-D, psychiatric co-morbidity^4^, disability days				
Healthcare Utilization	X	X	X	X
Mental healthcare utilization (receipt of antidepressant medication and/or counseling) General healthcare utilization (emergency room visits and hospitalizations)				
Healthcare Process	X	X	X	X
PDM with providers, visit-specific and overall satisfaction, satisfaction with case manager^5^, ratings of depression care management and intervention materials^6^				

**Audiotapes **(patient-provider communication)^7^	X			

CIDI = Composite International Diagnostic Interview, Depression Scale, CES-D = Center for Epidemiologic Studies Depression Scale, PDM = participatory decision making; ^1^measured at 12 and 18 months; ^2^measured only at 18 months; ^3^not measured at six months; ^4^Substance abuse, panic attacks, anxiety, and traumatic events; ^5^measured only at six and 12 months; ^6^measured only at 12 months only; ^7^collected at enrollment visit and after primary care provider intervention.

One modification to the original study protocol was made shortly after the 12-month follow-up was complete. Because the pattern of improvement differed between intervention groups at six months and 12 months of follow-up, a decision was made to extend follow-up to one additional interview at 18 months, and IRB approval was obtained to re-contact study patients. However, because outcomes assessors at 18 months were not blinded to intervention assignment, depression status at 12 months remains the study's primary outcome.

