The data on outcome variables fall into two broad categories: continuous variables, such as depressive symptom score (CES-D) [48] and functional status scores (MOS SF-12) [49], and dichotomous variables, such as depression remission status and receipt of guideline-concordant treatment. The primary ITT analyses are designed as regression modeling using patients as the unit of analysis, with each regression model structured to have a parameter designated for each visit where the outcome of the model was scheduled to be assessed, separately for each intervention group, so that the mean model is fully saturated for the intervention by visit parametrization. This parametrization allows estimation of mean differences observed within each intervention group betweeen baseline and a given follow-up visit for a continuous outcome, and odds ratios of having the outcome event at a given follow-up versus the baseline visit within each intervention group for a binary outcome, after adjusting for other covariates in the model. The evalution of patient-centered intervention effects will be conducted by testing the significance of difference of the adjusted mean differences, or the ratio of adjusted odds ratios, of a given follow-up versus the baseline visit between the intervention groups. The primary testing contrast is the baseline to 12-month change in outcomes between intervention groups; the models can easily accommodate additional data obtained by extending the follow-up to 18 months.

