Site and clinician characteristics are included as covariates in all regression models to account for potential patient outcome clustering within clinical sites and/or clinicians. To account for longitudinal correlations between outcome assessed over time within patients, mixed effects modeling appraches with unstructured correlation matrix are used whenever possible. Robust estimation is used for statistical inferences. The likelihood approach underlying the proposed mixed effects modeling would produce valid statistical inferences with missing data if the missing mechanism is Missing at Random (MAR) and the proposed mean and correlation models are correct. We thus anchor our ITT analyses on mean models with fully saturated visit by intervention parametrization plus all the covariates as necessary, paired with an unstructured correlation model to develop valid statistical inferences under MAR. We then conduct sensitivity analyses through multiple imputation under plausible missing scenarios that are non-MAR to examine the robustness of our inferences under such situations.

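### The claim of MAR-valid inference is not secured for remission: the instrument is not named, and a CIDI definition would leave nothing to carry a patient lost before 12 months

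*Protocol article*

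**What the plan says.** All references are to the protocol article.

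- **Outcomes covered.** Main outcome measures and statistical analysis plan places in one regression framework the continuous scores and the "dichotomous variables, such as depression remission status and receipt of guideline-concordant treatment". No instrument is given for remission.
- **One outcome per model.** Each model has "a parameter designated for each visit where the outcome of the model was scheduled to be assessed", separately by intervention group.
- **Binary contrast.** The model is to estimate "odds ratios of having the outcome event at a given follow-up versus the baseline visit within each intervention group for a binary outcome", and the groups are compared by the ratio of these odds ratios.
- **Missing data.** The section says that "mixed effects modeling appraches with unstructured correlation matrix are used whenever possible". It states that the likelihood is valid "if the missing mechanism is Missing at Random (MAR) and the proposed mean and correlation models are correct", and anchors the intention-to-treat analyses on the saturated mean model "paired with an unstructured correlation model to develop valid statistical inferences under MAR". The only imputation mentioned is for sensitivity: "We then conduct sensitivity analyses through multiple imputation under plausible missing scenarios that are non-MAR".
- **Schedule.** The Table 4 footnote on the CIDI reads "not measured at six months". The CES-D is listed at enrollment, six, 12 and 18 months. Specific aim two lists remission at six and 12 months.
- **Baseline status.** Under Eligibility criteria, every enrolled patient met criteria for one-year major depression on the structured interview.

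**The concern.** A likelihood model for repeated measures handles MAR dropout by borrowing from the outcome values that a patient did provide. The protection covers only what is in the model. If a patient's earlier values of that outcome are constant or not collected, there is nothing to borrow, whatever correlation structure is named.

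Remission may be in that position. The six-month CES-D is collected on the same patients and is a natural predictor of both dropout and 12-month remission, but a one-outcome model leaves it out. Dropout driven by observed six-month symptoms is MAR given everything collected, but not given what the remission model contains. If that mechanism or the dropout rate differs by arm, the remission contrast is biased under a mechanism that the article says its analyses handle. Remission is part of the main hypothesis. Differential dropout is also plausible, because participants could not be masked and the care managers' approach to engagement differs by arm.

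**Working it through.** The plan gives no figure on this point, so there is none to reproduce. The check has two parts.

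**1. What the remission model contains through 12 months**

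| Definition | Baseline | 6 months | 12 months | Patient missing at 12 months |
|---|---|---|---|---|
| CIDI | 0% in remission, by eligibility | not measured | measured | adds nothing |
| CES-D-based | from the score | measured | measured | adds six-month status |

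Under the CIDI definition:

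- The model reduces to patients with a 12-month CIDI.
- Baseline odds of remission are 0/(1 − 0) = 0, so an odds ratio of follow-up versus baseline divides by zero.
- Specific aim two's six-month remission comparison has no data.

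Under a CES-D-based definition, a saturated multinomial likelihood can be fitted. It was checked by simulation with 200,000 patients per arm, assumed remission at six/12 months of 35%/45% versus 50%/60%, latent correlation 0.6 and about 15% dropout depending on six-month remission. The 12-month log odds ratios were:

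| Dropout pattern | True | Completers | Binary likelihood |
|---|---|---|---|
| Six-month non-remitters drop out more, both arms | 0.61 | 0.65 | 0.62 |
| Opposite patterns in the two arms | 0.61 | 0.42 | 0.61 |

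The likelihood recovers the truth here because dropout depends on exactly the binary variable in the model. The next part lets dropout depend on the continuous score.

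**2. Size of the error when dropout follows the six-month score**

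- From Sample size considerations: 15% dropout by 12 months.
- Assumed, not in the documents: standard normal six- and 12-month scores with correlation 0.5 to 0.7; remission is a score below the median (50% in both arms, so the true difference is 0); log-odds of dropout rise by 1 per SD of the six-month score; unequal dropout rates where shown.
- Error = estimated minus true remission, with 1,000,000 simulated patients per arm. Ranges run over the correlations.

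| Scenario | Completers (points) | Model with six-month remission yes/no | Conditioning on six-month score |
|---|---|---|---|
| Within one arm, 15% dropout | 2.6 to 3.7 | 1.0 to 1.2 | 0 |
| Between arms, same rate and mechanism | 0 | 0 | 0 |
| Between arms, 20% vs 10%, mechanism in both | 1.7 to 2.3 | 0.6 to 0.7 | 0 |
| Between arms, 15% each, mechanism in one | 2.6 to 3.7 | 0.9 to 1.2 | 0 |
| Between arms, 25% vs 10%, mechanism in the 25% arm | 4.2 to 6.0 | 1.5 to 1.9 | 0 |

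Zeros are zero to within simulation error (0.1 point). The yes/no model keeps about a third of the completer error (for example 1.9/6.0 = 0.32). Conditioning on the score removes it.

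**Yardstick.** With 132 patients, assumed equally split, and 15% dropout: 66 × 0.85 = 56 per arm. The standard error of a difference at 50% is √(2 × 0.5 × 0.5/56) = 0.094, or 9.4 points before clustering.

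**The case against.** Several points on the other side stand.

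- **Binary likelihoods exist.** A reader might infer that an unstructured likelihood model cannot be fitted to binary outcomes, so that the MAR claim fails for all of them. That is not so. Multivariate probit and saturated multinomial models do this, and the second was fitted above. Which binary model is used is a detail that an article may leave to the full plan.
- **The CIDI definition is not stated.** A reader might infer it from the CIDI's diagnostic role, but no section says it. Listing remission at six months fits a CES-D definition better.
- **The claim is qualified.** It is conditional on MAR and on correct models, the mixed model is used only where possible, and non-MAR imputation is planned. No marginal (GEE) fallback is named, so its known weakness under MAR cannot be charged to the plan.
- **Completer analysis is not always biased.** It is valid if missingness depends only on arm and modelled covariates. An 18-month CIDI could also bring back a patient missed at 12 months.
- **Treatment receipt is not affected by the gap.** Health care utilization is scheduled at every visit.

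What remains is narrower. The claim covers remission without exception, six-month symptoms are not among the stated covariates, and the planned imputation addresses only non-MAR scenarios. The 18-month interview was added after 12-month follow-up was complete, its assessors were not blinded, and it helps only patients who returned.

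**Conclusion.** The point holds in conditional form. The article claims MAR-valid inference for its intention-to-treat analyses as a group, without fixing what remission is or showing that its model carries the information the claim needs. Under a CIDI definition, the analysis through 12 months is a completer analysis with an undefined baseline contrast, and it contradicts the six-month remission aim. Under a CES-D definition, the model works but removes only part of the bias when dropout follows the continuous score.

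The between-arm error is 0 with equal rates and mechanism, about 2 to 4 percentage points in moderate scenarios and up to 6 in the extreme one, for completers. About a third of that remains when the model uses six-month remission only. These sizes rest on assumed correlations, dropout slopes and rates, and they are modest beside a standard error of about 9 points. It would go too far to infer that the trial's main result is at risk: the primary outcome is change in CES-D, which has a six-month value, and its analysis is unaffected. The change is worth making because it is cheap and helps under either definition.

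**What to change.** 1. State which instrument and rule define remission, and reconcile this with Specific aim two, the CIDI footnote to Table 4 and the binary contrast in the statistical section.
2. For remission, multiply impute missing 12-month status under MAR, within arm, from baseline and six-month CES-D, SF-12 and treatment.
3. Compare the arms directly at 12 months, rather than by a ratio of odds ratios against baseline.
4. Build the planned non-MAR scenarios as departures from that imputation.
5. For binary outcomes, limit the MAR claim to analyses that use this imputation or a full-likelihood binary model.

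The cost is some extra analysis work and reliance on the imputation model. No new data are needed, and multiple imputation is already planned for the sensitivity analyses.

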#### Sample size considerations

One of the major hypotheses to be tested is that improvements in CES-D scores for depressed patients in the patient-centered intervention group will be greater than those in the standard intervention group. Previous studies of treatment of depression in primary care using similar interventions (excluding the patient-centered and cultural adaptations) have shown remission and symptom improvement differences between intervention and usual care groups of 20 to 30% [19,20]. Our resources and available recruitment pools allowed us to aim for 15 clinicians and 125 patients per group, with an average number of 8.3 patients per physician (cluster). By assuming a within-cluster or intra-class correlation of 0.1 [50] and 15% dropouts by the end of 12 months follow-up (reflected using the variance inflation factor), a correlation between the baseline and 12 month CES-D score of 0.5, a mean CES-D score of 30 points at baseline for both intervention groups, 25% score reduction (*i.e*., 7.5 points) by 12 months in the standard intervention group, and the common cross-sectional SD for CES-D of 10 points for both intervention groups at both visits, we would have 80% statistical power to detect a between-group difference of 3.6 points or more in improvement in mean CES-D score at one year using a two-sided test with Type I error of 0.05. That is, if we expect to see a 7.5 point improvement in mean CES-D score for the standard intervention group after one year, then we would have 80% power to detect a 11.1 points or greater improvement in mean CES-D score for the patient-centered intervention group after one year.

Ethics and Consent

The trial received approval from the Johns Hopkins and MedStar Health Institutional Review Boards. Informed written consent was obtained from all participating clinicians and patients. Subjects were free to withdraw from the study at any time, to refuse to answer any question, and to either stop audiotaping or to have audiotapes of any visit dropped from the study. None of the patient information was released to their clinician, health care organization, or any other party without the patients' permission. Phone contacts to locate the study subject did not suggest the content of the study. All study data were stored in locked file cabinets at Johns Hopkins and not the clinical sites. Personal identifiers were removed as soon as possible. Audiotape data were transferred onto CD-ROMs for coding purposes, and stored in locked files after identifiers were removed. A code key is kept in a separate location restricted to the principal investigator and project director. Each clinician received an incentive of $200 paid to them individually or to their organization and each patient received $25 for completing each interview.

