#### Baseline characteristics of patients

Research assistants approached 1,486 patients for eligibility in waiting rooms between October 2005 and August 2006; 613 refused to complete in-person screening and 642 were determined to be ineligible by the first-stage screener (*e.g*. 457 were not depressed, 68 were positive for alcohol or drug abuse by the CAGE AID [51,52], and 46 were currently seeing a mental health specialist). Of the 231 patients eligible for the second-stage screen, conducted by telephone, 35 refused to complete it when called, 22 were unable to be reached to confirm their eligibility, and 42 were categorized as ineligible by the second-stage screen (CIDI). (Figure 3) Table 6 shows baseline characteristics of the 132 patients enrolled in the study. These patients are 46.4 years on average; 80% are women and 100% are African-American (4% also report being of Hispanic ethnicity). Forty-nine percent are high school graduates. The average annual household income is $41,393; however, 28% find it very difficult to pay their monthly bills. Fifty-eight percent are employed, and 89% have health insurance. The mean scores on the CES-D, MCS-12, and PCS-12 at baseline are 29.84, 36.18, and 42.12, respectively. Fifty-six percent of the sample reported having to take at least one disability day in the preceding two weeks.

**Table 6 T6:** BRIDGE study: Baseline demographic and clinical characteristics for 132 African American patients

Characteristic	Number of patients (%)	Mean (standard deviation)
Age, years, mean (SD)		46.4 (11.1)
Gender, female	105 (79.6)	
Ethnicity		
Hispanic	5 (3.8)	
Non-Hispanic	127 (96.2)	
Marital status, married	36 (27.3)	
Education		
< High school graduate	12 (9.0)	
High school	65 (49.2)	
Some college	50 (37.9)	
College graduate	5 (3.8)	
Annual household income		$41,393 ($26,840)
Employed		
Full-time/part-time	77 (58.3)	
Other^1^	55 (41.7)	
Healthcare insurance Payer	117 (88.6)	
Medicaid	21 (18.0)	
Medicare	25 (21.4)	
Other	82 (70.1)	
CES-D score		29.84 (14.09)
MOS-SF-12, physical component		42.13 (13.2)
MOS-SF-12, mental component		36.18 (12.6)
Comorbid medical condition		
Diabetes	46 (34.9)	
Hypertension	72 (54.6)	
Trouble breathing	33 (25.0)	
Back problems	40 (30.3)	
Arthritis/rheumatism	56 (42.4)	
Had one or more disability days in last two weeks	74 (56.1)	
Taking antidepressant medication	101 (76.5)	
Treated for depression at most recent visit	65 (49.2)	

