Limitations of the study should be discussed. The cluster design presents unique challenges with regard to comparability of groups (at the cluster and individual patient level), allocation concealment, maintenance of ITT principles, empty clusters, and participant switches from one cluster to another [55]. Several strategies have been recommended to overcome recruitment challenges: monitoring cluster guardian (*e.g*., practice leader) adherence to the study protocol before randomization of the cluster; including at least one patient participant before randomizing a cluster; and using recruiters who are blinded to participant allocation status. In this study, there was loss to follow-up among randomized clinicians before patient recruitment, which led to empty clusters (*e.g*., clinicians who did not contribute patients to the study) and failure to reach the recruitment target among patients, which may compromise the study's statistical power to detect differences in the primary outcome. Due to the staff resources available for recruitment and time frame needed for delivery of the clinician interventions, it was not feasible to delay randomization of clinicians until the first patient in each cluster was recruited. However, recruiters in this study were blinded to the allocation status of each cluster and its patients. With regard to analysis challenges, empty clusters and patients who switch from one cluster to another may lead to violation of the ITT principle. Recommendations include taking into account both clusters and individuals that withdraw or are lost to follow-up by using *ad hoc *missing data methods; keeping clusters as they were randomized, and using adjustment or propensity-score methods to deal with potential imbalances in both cluster and individual characteristics. In addition to these strategies, we will conduct sensitivity analyses to examine the potential impact of deviation from assumptions underlying such analytic approaches on the robustness of the study findings. Another design constraint is the limited ability to identify which aspects of the multi component interventions are most effective; we intend to conduct *post-hoc *analyses to determine whether the number of intervention contacts, use of intervention materials, and rating of intervention effectiveness by clinicians and patients are related to study outcomes.

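### The stated 80% power for a 3.6-point CES-D difference does not follow from the listed inputs under the usual design-effect calculation, which gives about 4.9 to 5.1 points, and the power lost in the enrolled sample is not quantified

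*Protocol article*

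**What the plan says.** Under Sample size considerations, the protocol article says resources allowed the team to "aim for 15 clinicians and 125 patients per group", averaging 8.3 patients per clinician. The calculation is introduced with "By assuming a within-cluster or intra-class correlation of 0.1 [50] and 15% dropouts by the end of 12 months follow-up", and the dropout is said to enter through a variance inflation factor. The remaining inputs are a baseline to 12-month correlation of 0.5 and a cross-sectional SD of 10 in both groups at both visits. The claimed result is "80% statistical power to detect a between-group difference of 3.6 points or more in improvement in mean CES-D score", "using a two-sided test with Type I error of 0.05". The section restates this as an improvement of 11.1 points against 7.5.

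Main outcome measures and statistical analysis plan makes the primary test the between-group difference in change from baseline to 12 months.

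Under Baseline characteristics of patients, "Table 6 shows baseline characteristics of the 132 patients enrolled in the study"; that table gives a baseline CES-D SD of 14.09. The Discussion mentions empty clusters and "failure to reach the recruitment target among patients, which may compromise the study's statistical power", with no revised figure.

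**The concern.** Everything a standard calculation needs is listed, so the 3.6 can be checked. It lies close to what an individually randomised trial with no dropout would detect, although an ICC, a cluster size and a dropout rate are all named as inputs. Enrolment then reached 132 patients instead of 250, and the baseline SD was about 40% above the planned value (14.09 / 10), yet the only detectable difference in the article is still 3.6.

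This is the power statement for the primary outcome. Both arms are active programmes, so a reader who trusts 3.6 would think that true differences of 4 to 8 points had been well tested when they had not.

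**Working it through.** **Inputs** (Sample size considerations unless noted): n = 125 per arm; m = 8.3; ICC = 0.1; dropout 15%; r = 0.5; SD = 10; two-sided 0.05; power 80%. Contrast: difference in change (Main outcome measures and statistical analysis plan).

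**Formulae**
- Change SD = sqrt(2 × 10² × (1 − 0.5)) = 10.
- Detectable difference = (1.960 + 0.842) × SD × sqrt(2 × DE / n).
- Completers per arm = 125 × 0.85 = 106.25.
- Design effect (DE) = 1 + (8.3 − 1) × 0.1 = 1.73, or 1 + (8.3 × 0.85 − 1) × 0.1 = 1.61 at the retained cluster size.

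**Attempt to reproduce 3.6**

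| Allowance made | n per arm | DE | Detectable difference | Power at 3.6 |
|---|---|---|---|---|
| None | 125 | 1 | 3.54 | 81% |
| Dropout only | 106.25 | 1 | 3.84 | 75% |
| Clustering only | 125 | 1.73 | 4.66 | 58% |
| Both | 106.25 | 1.61 | 4.87 | 54% |
| Both | 106.25 | 1.73 | 5.06 | 51% |

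Inflating for dropout by 1.15 instead of dividing by 0.85 gives 4.82 to 5.00. A baseline-adjusted analysis (SD = sqrt(75) = 8.66) with both allowances gives 4.22 to 4.38.

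Solving backwards, DE = (3.6 / 28.02)² × n / 2. This is 1.03 at n = 125 and 0.88 at n = 106.25. With the stated dropout, clustering would have to reduce the variance.

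**Sample size for 3.6.** Without allowances, 2 × 100 × 2.802² / 3.6² = 121.1 per arm. Multiplying by 1.61 / 0.85 or 1.73 / 0.85 gives about 229 or 247.

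**A route that does reach about 3.6.** Suppose the clinician effect is constant over time, so that it cancels in the change score, and 0.5 is the correlation within clinician. The change variance is then 2 × 100 × (1 − 0.1) × (1 − 0.5) = 90.
- Dropout as × 1.15: 2.802 × sqrt(2 × 90 × 1.15 / 125) = 3.61 (79.9% power at 3.6).
- Dropout as / 0.85: 2.802 × sqrt(2 × 90 / 106.25) = 3.65 (79.0%).
- With 0.5 as the plain correlation, variance 100: 3.80 and 3.84 (about 75%).

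**Enrolled sample.** Assumptions: 66 per arm (the text gives no patient split) and r, ICC and dropout carried over. Of 36 clinicians randomised, eight contributed no patients (Baseline characteristics of the clinicians). That leaves 28, or 27 if the clinician who left before baseline is counted separately. Completers per arm = 66 × 0.85 = 56.1. DE is 1.30 to 1.39 over these clinician counts and the two cluster-size conventions.
- SD 10: 6.03 to 6.23.
- SD 14.09 at both visits: 2.802 × 14.09 × sqrt(2 × 1.30 / 56.1) = 8.50, rising to 8.78 at DE 1.39. Power at 3.6 is 21 to 22%.
- SD 14.09, ICC 0, no dropout: 2.802 × 14.09 × sqrt(2 / 66) = 6.87.
- SD 14.09, patients split 15:21 like the clinicians, DE 1.39: 8.91.

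**The case against.** The strongest reply is that 3.6 can be obtained from the listed numbers. The section does not say that its ICC is an ICC of change scores, and a stable clinician effect does cancel in the planned contrast. The 3.61 route uses the ICC, the dropout and the correlation, and it rounds to the stated figure. This stands as arithmetic: 4.9 to 5.1 is the usual reading, not the only possible one.

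It does not rescue the text as written. The route needs two unstated assumptions, gives the stated cluster size no role, and has the ICC lower the variance, which fits poorly with a variance inflation factor. With 0.5 taken as the plain baseline to 12-month correlation, the result depends on how stable clinician effects are between visits. At the retained cluster size it runs from 3.84 (fully stable) through 4.87 (clinician-effect autocorrelation 0.5) to 5.72 (autocorrelation 0), and never reaches 3.6.

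A reader might infer that clustering and dropout were simply left out. The documents do not show that: the unadjusted figure is 3.54, which rounds to 3.5, and the article does not report its formula.

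A reader might also take 8.5 points as the trial's established detectable difference, or treat the missed target as an error in the calculation. Neither is supported. The section is prospective, the Discussion discloses the shortfall, and 8.5 depends on a baseline SD applied at 12 months, an equal split and carried-over inputs. With fully stable clinician effects and 15% dropout, the same SD gives 7.1 to 7.5. Finally, the article nowhere says that a non-significant result would mean equal effectiveness. A sentence on interpreting the confidence interval would be a reporting preference, not a correction.

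**Conclusion.** The power statement is not supported by the assumptions as written. Under the usual design-effect calculation, the planned trial had 51 to 54% power at 3.6 points. This rests on applying ICC 0.1 to the change score and reading 0.5 as the plain correlation. The gap closes only under the two unstated assumptions.

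For the enrolled sample, what is missing is the size of the power loss, not its disclosure. The size is conditional: about 6.0 to 6.2 points at SD 10, and about 6.9 to 8.9 if SD 14.09 applies at both visits. Within the latter range, ICC 0.1 and 15% dropout give about 8.5, with about 22% power at 3.6. Even the most favourable case in that range, with no clustering and no dropout, is nearly twice the stated 3.6.

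**What to change.** - In Sample size considerations, restate the detectable difference for the planned 30 clinicians and 250 patients as about 4.9 to 5.1 points and change the 11.1-point illustration to match. Alternatively, keep 3.6 and state the formula, the assumed stability of clinician effects over time and which correlation the 0.5 is.
- In the Discussion, replace the remark that power may be compromised with the conditional range for 132 patients given above. State the assumed equal patient split, the carried-over correlation, ICC and dropout, and that no 12-month SD is reported.

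The cost is a short recalculation and a few sentences. No extra patients and no change to the design, endpoint or analysis are needed; the drawback is a less favourable stated figure.
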